### Ethics approval and consent

This study has received approval from the Institutional Review Board of Columbia University Medical Center and the Kintampo Heath Research Centre Institutional Ethics Committee. The study is registered with clinicaltrials.gov under NCT03352830. Informed consent is obtained by KHRC fieldworkers from all ELAG study participants prior to enrollment.

### Power

Power calculations reflect the cluster-randomized study design. Treatment is on the cluster level (2) while outcomes are on the household level (1). The outcome of the study is minutes of LPG use per day summed over a six-month period. Multilevel model power calculations with 27 clusters, 979 sample size and type I error at 5%. The mean for the reference group is estimated at 3000 min over 6 months, with equal group sizes. This is believed to be a conservative estimate based on our unpublished research in the region, which found ~ 3100 mean minutes of use over 20 weeks [42]. The effect size (Cohen’s D) is calculated with 1000 min as the pooled standard deviation, which is an overestimation based on our research. Multilevel power formulas were derived from Scherbaum, 2009 [43]. Intraclass Correlation Coefficients are unknowable given the novelty of the research, but several possibilities were modeled - visualized with the Optimal Design Plus Empirical Evidence version 3.1 software, see Fig. 2.

**Fig. 2 Fig2:**
[figure not shown]
Power Calculations at .3 and .5 effect sizes

### Health promotion intervention

The study consists of two types of interventions, a behavioral change intervention and an access intervention. Our team selected the Risks, Attitudes, Norms, Abillities, and Self-Maintenance (RANAS) model to design a clean cookstove behavioral change intervention [37]. The RANAS model was originally designed and employed for issues pertaining to water, sanitation, and hygiene. However, we recognized its potential application for clean cookstove adoption. The core assumption that underpins the RANAS model is that each of these five behavioral factors are necessary, but not sufficient, to induce behavior change. After baseline data collection, ELAG households will be convened in cluster-wide meetings for LPG stove distribution and the behavioral change intervention. A research team member and a peer-adopter will collaborate to deliver the intervention. The peer-adopter is a participant from a GRAPHS LPG community who has maintained use of LPG after study conclusion. ELAG will rigorously employ RANAS to promote clean cookstove adoption, see Additional file 1 for the scripts used to guide the interventions.

Like other behavioral change campaigns, RANAS involves communicating risks associated with the traditional behavior. Not only should participants be aware of the severity of risks, but they should be made to recognize that they are vulnerable to those potential health outcomes [25, 44, 45]. Participants are first introduced to the concept of HAP. Then they are presented with a series of pictures that show adverse outcomes that have been shown to be caused by HAP, and that are recognizable to community members (cataracts, low birth weight, and respiratory diseases) [3, 7]. Additionally, pictures of blackened kitchen walls are used to explain that the same pollutants which dirty the walls also enter human lungs when exposed to smoke.

Attitudinal factors include perceptions of time, money, and effort associated with the behavior change, and the benefits of the new behavior. Following the presentation of risks, participants will be informed of the potential health benefits of reduced HAP exposure. Other benefits will be presented, such as reduced time dedicated to wood collection which can then be reallocated for educational or economic goals [46].

Normative factors describe perceived expectations from peers, leaders, and/or of one’s self. At this point the LPG peer adopter provides a testimonial regarding their experiences using LPG and overall appreciation of the technology. This is complimented with the a research staff explaining the Ghanaian government’s efforts to reduce HAP-exposures and protect Ghanaian natural resources from deforestation [47]. The community is then prompted to make a collective commitment to using LPG.

The ability-related behavioral factor represents the participants’ confidence in performing the new behavior. These abilities include safe, effective, and culturally-appropriate use of an LPG stove, which may require some orientation. Indeed there is some literature that documents new user’s reticence to use a new stove because it is unclear how culturally suitable it is [48, 49]. Therefore, it is important to demonstrate how to cook traditional Ghanaian meals on the LPG stoves. An LPG peer adopter will have a food demonstration where they cook a traditional meal for the participants in that cluster. On a longer timeframe, individuals may be unsure how to sustain the repeated payments required to refill the LPG cylinder [48, 50]. The intervention will also include a financial literacy orientation, which will provide strategies on how to smooth payments over time, including savings strategies and credit. A key component of the orientation will be a discussion among participants in smaller groups, on different scenarios of household financial limitations and the different strategies they would use to meet the financial obligation of using LPG stoves. Participants will also be provided with *susu* boxes (savings boxes) and encouraged to make weekly deposits towards the refilling of LPG cylinders.

Self-regulation factors provide continued orientation to the desired behavior in anticipation of conflicts or distracting cues to the old behavior. The self-regulation factor is designed with the assumption that relapse to the old behavior is inevitable for many individuals because outside circumstances cannot be controlled. ELAG addresses this factor by contracting and training Community-based Surveillance Volunteers (CBSVs) who will visit participants weekly to discuss the potential barriers to sustained use and brainstorm possible solutions. This is to assist sustained use efforts throughout the study period. CBSVs are trained to recognize and assist with issues that would interfere with LPG use, and serving overall as a resource for households. CBSVs have a long-standing presence in the communities, charged with tracking health and demographics in each community.

### Access intervention

Policy makers and researchers have suggested the importance of the ‘last mile’ (or, more realistically in rural Ghana, last 30 km [42]) of LPG delivery/accessibility, but few have empirically demonstrated the degree to which logistical barriers impact user demand [51–53]. This intervention will determine the degree to which physical accessibility of a product influences sustained use. Each community has at least one taxi driver or motor-king (tricycle cart) rider who can be paid to transport individuals or goods. KHRC will contract such drivers/riders in each community to provide pickup and drop off services for LPG cylinders. For this study, households in access intervention clusters will bear the cost of the refilling while the cost of transportation will be paid for with vouchers provided by the study. This intervention addresses an important gap in our knowledge surrounding sustained demand and use patterns of LPG fuels.

### Factorial design

Each cell of the factorial design will be functionally treated as an ‘arm’ of the study, see Table 1. This means that no one group will experience exactly the same set of conditions. The ‘No educational intervention’ and ‘No agent delivery’ will serve as the control group, while all other permutations of the two interventions will be compared to the control group during the analysis phase. As per the parent study (GRAPHS), this is a cluster randomized control trial. Randomization will occur on level 2 (villages) while outcomes will be measured at level 1 (households).

### Randomization

The parent study utilized a cluster-randomized design on coarsened exact matches to assign study treatments [54]. This study re-randomized clusters employing a covariate-constrained randomization approach with several identified prognostic covariates [55, 56]. The covariate-constrained randomization approach is a powerful allocation technique to ensure balance between arms in cluster randomized trials. Baseline covariates were chosen based on prior literature and theoretical relationships (see Table 2). When covariates are continuous, balance is determined via mean differences between treatment arms. Maximum permissible imbalance is designated a priori. Given these parameters, allocation amongst arms is randomly designated if below the maximum permissible imbalance. An independent epidemiologist performed the final randomization using the *ccrand* procedure in Stata [57]. Allocation was not revealed to field staff until after baseline data collection was complete.

**Table 2 Tab2:** Covariate constrained randomization variables

Variable	Rationale
Community Asset Index	Scientific articles have shown that differential access to resources can be predictive in the uptake of new cookstove technologies (19–21).
Average Household Size	Scientific articles have shown that household size can be predictive in the uptake of new cookstove technologies (19–21).
Distance to Refueling Station	Study communities are scattered throughout the region at varying distances from the refueling center. Further distances are likely a deterrent to refuel for non-Agent delivery households, *see map*.
Households per cluster	To ensure roughly equal number of participating households per arm.

### Stopping guidelines

#### Positive stopping rule

Due to the nature of the intervention, the outlined study does not have a positive stopping rule. The hypothesis is that an educational intervention and an agent-delivery system will meaningfully increase sustained use of the clean cookstoves. Identifying the significance and magnitude of that improvement is a policy-relevant endeavor as it affords the opportunity to conduct cost-benefit analyses of expanded implementation. Our current outcome measure is time-dependent, wherein we will compare cookstove usage over the 12 months of the intervention.

#### Negative stopping rule

This is a behavioral intervention designed to determine effective strategies to increase the uptake of clean energies. The control group is a ‘business-as-usual’ approach, and we hypothesize the intervention groups will improve their uptake of the new technologies. We plan to halt study activities if 1) there are any LPG cookstove-related accidents that occur within our cohort and the study timeframe that result in permanent bodily injury or death, or (2) if the intervention groups show statistically significant decreases in LPG cookstove usage.

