### Challenges in cookstove adoption research

Studying cookstove adoption is both conceptually and methodologically challenging. Disciplines involved span the social, environmental, and health sciences, utilizing quantitative, qualitative, and mixed methods [26–30]. The field has largely employed observational study designs to date. While these studies are quite informative, they may be vulnerable to selection bias because individuals opt into each group of the study by deciding whether or not to purchase a stove, sustain use, etc. There may be underlying characteristics that predict entry into each group, thus limiting the generalizability of findings. Controlled trials can address these limitations through the randomization and follow up of participants, but there are few studies utilizing these study designs [31, 32].

Most cookstove adoption studies have focused on initial adoption versus sustained use. [21, 33]. This is an important distinction because adoption studies have largely focused on the enablers and barriers of initial stove acquisition and/or the use of the technology early in its adoption [13]. However, there are many reasons to believe that behaviors change over time. For example, researchers have noted situations wherein new stove use is high upon acquisition, but decreases over time. There are plausible reasons why participants would decrease use. New stoves could break with consistent use, and without access or means of repair, participants would likely default to the traditional stove. It is also possible that a household’s financial circumstances change and use falters. Without clear plans to recover from these external stimuli, users would resume traditional stove use. While there is a small number of studies focused on sustained use, that amount is growing. This is because researchers increasingly recognize the importance and complexity of the issue [13, 34, 35].

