### Outcome measures

The principal outcome of interest is minutes of LPG stove use over the last 6 months of the study. This time period is of interest in order to assess the effectiveness of the intervention on sustained use rather than initial adoption. Stove use will be measured via stove use monitors (SUMs). Each stove will be equipped with SUMs, which are iButton temperature loggers programmed to collect temperature data at 10 minute intervals [64]. This leaves the memory at capacity after 2 weeks. Field staff will visit households every 2 weeks to download the data. Monitors will be used to determine minutes of stove use during that period. Biweekly visits will also serve as a quality control measure because staff can address faulty readings, typically by replacing the iButton.

A secondary outcome of interest is stove use measured via weighing of LPG cylinders with a scale. Field staff are scheduled to visit households every 2 weeks to download SUMS data. They will use this opportunity to administer an LPG stove use questionnaire and weigh cylinders with a scale during their bi-weekly visits. Weighing cylinders is a cheaper alternative to measuring stove use, but it is possible that the measurements are biased. When a cylinder is weighed, participants will be asked if they refilled the cylinder within the 2 weeks and, if so, how much. It is possible that social-desirability bias is introduced in these measurements because participants are aware of our study interests and may misreport accordingly [65]. Determining the degree of bias or measurement error by comparison to SUMS data may be useful for future studies requiring stove use measurements in Ghana or similar contexts. See Fig. 3 for a study timeline.

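### The usage stopping criterion halts the study on ordinary statistical significance without stating the comparator, time window, significance level or number of looks

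*Protocol article*

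**What the plan says.** All references are to the protocol article.

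- **Negative stopping rule.** The consequence is stated plainly: "We plan to halt study activities if" either of two conditions is met. The second is the usage condition, "if the intervention groups show statistically significant decreases in LPG cookstove usage". Shortly before it the text notes that "The control group is a ‘business-as-usual’ approach", but the condition itself names no comparator.
- **Positive stopping rule.** The article has none, and no interim analysis plan is described there.
- **Factorial design.** "all other permutations of the two interventions will be compared to the control group during the analysis phase". The Analysis section likewise compares three intervention arms with control. Both statements concern the final analysis.
- **Power.** The only error rate given belongs to the sample size calculation: "979 sample size and type I error at 5" per cent, with no sidedness stated.
- **Outcome measures.** Usage data are downloaded every two weeks. The primary outcome is LPG use in the last six months, and the reason is given: "This time period is of interest in order to assess the effectiveness of the intervention on sustained use rather than initial adoption".
- **Challenges in cookstove adoption research.** The background mentions reported situations in which "new stove use is high upon acquisition, but decreases over time".

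**The concern.** A rule that ends a study should say which contrast is tested, in which period, against what threshold and how often. This one gives only statistical significance and a direction, so two people applying it in good faith could reach opposite decisions from the same data.

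There are two possible readings, and each has its own problem.

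- **Decrease relative to control.** The test has no stated level and no limit on repetition. Chance alone could stop the study, the more readily the more often it is applied and the more arms are tested separately.
- **Decrease over time within the intervention groups.** A fall that also occurs in control, or is larger there, would still meet the condition.

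The primary outcome is use in months 7 to 12. A halt of study activities before month 7 would therefore leave no primary outcome, and would rest on the initial-adoption period that the article distinguishes from its main question.

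**Working it through.** The article gives no error rate, boundary or look schedule for this rule, so there is no figure to reproduce. The calculations show what the wording allows.

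**Reading 1: intervention against control, no true effect**

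Inputs from the article: three intervention arms against one control; data every two weeks for 12 months, so at most about 52/2 = 26 looks. Assumptions: 1 to 26 equally spaced looks; each look tests cumulative data at the lower 2.5% tail (5% two-sided, adverse direction only); arms of equal size; normal test statistics.

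Let *s* be the share of per-period variance in an arm mean that persists over time (stable cluster differences). At look *k* the standardised arm mean is

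X(k) = [b + mean(e₁…e_k)] / √(s + (1 − s)/k), with Var(b) = s and Var(e) = 1 − s.

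The contrast is Z(k) = [X_arm(k) − X_control(k)] / √2, and a false halt occurs if Z(k) < −1.96 at any look. Results from 40,000 simulated trials per cell:

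| Looks | One contrast, s = 0 / 0.5 / 0.9 | Any of three arms, s = 0 / 0.5 / 0.9 |
|---|---|---|
| 1 | 2.5% (nominal) | about 6% |
| 2 | 4.1 / 3.7 / 2.9% | 10.5 / 8.9 / 7.5% |
| 4 | 6.3 / 4.7 / 3.2% | 14.8 / 11.2 / 8.5% |
| 12 | 10.5 / 5.7 / 3.7% | 23.4 / 13.5 / 8.8% |
| 26 | 13.6 / 6.0 / 3.7% | 29.0 / 14.3 / 8.9% |

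The column s = 0 (independent increments) gives upper values. Stable village differences correlate successive looks and lower the figures. At 12 to 26 looks the range is about 4–14% for one contrast and 9–29% for any of three arms.

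**Reading 2: later against earlier use within the intervention groups**

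Inputs from the article: 979 − 271 = 708 intervention households in 7 + 7 + 6 = 20 clusters (Table 1); mean 3000 minutes and SD 1000 minutes over six months (Power). Assumptions: ICC 0 to 0.10; between-period correlation *r* of 0 or 0.5.

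- Design effect: DE = 1 + (708/20 − 1) × ICC = 1 + 34.4 × ICC.
- SE of the change: 1000 × √[2(1 − r)] × √(DE/708).
- Probability of significance: Φ(fall/SE − 1.96).

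For a 10% fall (300 minutes):

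- Least favourable case, ICC 0.10 and r = 0: DE = 4.44, SE = 112.0, 300/112.0 = 2.68, Φ(0.72) = 76%.
- Most favourable case, ICC 0 and r = 0.5: DE = 1, SE = 37.6, 300/37.6 = 7.98, probability above 99%.

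A 20% fall (600 minutes) gives at least 600/112.0 = 5.36, so above 99% throughout. A 5% fall gives 27% to 98%. None of these depends on the control arm.

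The SD applies to six-month totals, so this is an illustration. A halt during follow-up would compare shorter windows, for which the article gives no SD.

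**The case against.** The strongest reply is that context supplies the comparator. The text sets the control group against the intervention groups just before stating the rule, and every planned arm comparison is with control. There is also no earlier study level from which a decrease could be measured, since "ELAG households will be convened in cluster-wide meetings for LPG stove distribution and the behavioral change intervention". This largely stands: control is the more natural reading, and on it a decline common to all arms would not trigger a halt. But the sentence does not say so, and the lack of a pre-intervention level does not exclude comparing later with earlier use.

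Further points that stand, in whole or part:

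- **Decline is not stated to be expected.** A reader might infer that the article predicts a fall and so has written a rule that is bound to fire. It does not. The background reports only that such falls have been noted in some situations.
- **Three arms and many looks are assumed.** The rule refers to the groups in the plural and could mean them together. The two-weekly visits are for download and quality control, and the monthly reports cover enrolment and field activities. Neither is described as a comparative analysis of usage.
- **An early look is not wrong in itself.** A harm criterion need not wait for the primary window, and the article also plans to analyse the first five months.
- **Detail may sit elsewhere.** A look schedule or boundary could be in a fuller protocol or analysis plan that is not shown, and its absence from an article would not be a finding. The point here is different: the article publishes the halting condition itself, and as published its contrast is undefined.
- **It is headed as a guideline, and it does not inflate efficacy claims.** Both are true. They limit the harm but do not make the trigger interpretable.

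**Conclusion.** The point holds in a limited form. The usage criterion rests on ordinary significance with comparator, window, level and number of looks unstated, and no other section supplies them for this rule.

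Its size depends on how the rule would be applied. Against control, the false-halt chance is 2.5% for one contrast at one look and about 6% if each of three arms is tested once. With 12 to 26 looks it becomes about 4–14% for one contrast and 9–29% for any of three arms. These figures assume unadjusted testing at a one-directional 2.5%, and the number of looks is not in the article. It would be wrong to cite 23% or 29% as the rule's error rate: those values need separate testing of three arms, at 12 or 26 looks respectively, and no persistent cluster differences.

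On the within-group reading, a modest decline could well trigger a halt even if the interventions beat control. Since that is the less natural reading, it is a reason to close the ambiguity and not a prediction that the study will stop.

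The criterion should be corrected. The accident criterion was not assessed.

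**What to change.** Reconcile the Negative stopping rule with the Challenges, Factorial design, Outcome measures and Analysis sections by restating the usage criterion alone:

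1. The quantity is the difference between intervention and concurrent control over the same calendar window, estimated from the planned hierarchical model. State whether arms are tested separately or together.
2. It is examined at one or two pre-set looks, against a strict boundary stated in advance, for example of Haybittle–Peto type at p < 0.001.
3. Crossing the boundary prompts review and does not halt the study automatically.
4. Change over time within the intervention groups is not a trigger.

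If the boundary is one-directional, three arms at two looks give a false-trigger chance of at most 3 × 2 × 0.001 = 0.6%.

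The change takes about two sentences. Its price is slower reaction to a moderate adverse usage difference. The final significance level is unaffected, because the rule can only stop for worse use. The accident criterion is left as it is.

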### Baseline data collection and covariates

Information on several constructs will be collected before delivering the behavioral and infrastructural interventions. Beyond standard baseline demographic and socioeconomic status surveys, a pre/post-test of RANAS model behavioral factors will be administered in order to document any changes in participants knowledge, perceptions, or attitudes regarding HAP and/or LPG stoves [25, 44, 45]. This will provide vital insight on the role of household/setting characteristics on sustained use, and the effectiveness of the various components of the behavioral intervention on knowledge/perceptions of HAP and cookstoves.

Many studies have shown that gender can play an important role in predicting cookstove adoption [58, 59]. Intra-household cooperation is a conceptual framework that makes explicit the bargaining process of decision-making within a household. Contrary to earlier economic theory, households do not operate as a unit. Instead, several actors negotiate decision-making, and power is rarely symmetrically distributed within the household [60, 61]. This asymmetry tends to follow gendered power dynamics. The concept of intra-household bargaining could thus mediate the relationship between the intervention and increased sustained use. Our study will utilize a modified version of the dictator game to assess intra-household cooperation [62, 63]. The game requires each partner of the household be separated temporarily for administration. Once separate, they are asked to select one of three envelopes with different pre-portioned sums of money. They must then decide whether to keep the entire sum of money for themselves, or direct all or a portion of it to their spouse and/or charity. The player can chose to send a certain amount of money to the third party. The money has a 50/50 chance of reaching that party and, if so, being doubled. In a perfectly cooperative household, it is within each individual’s interest to send all of the money to their partner. Intra-household cooperation, then, is measured as the ratio of money sent between partners over the entire amount received. Note that payout is hypothetical and currency will not actually exchange hands.

LPG fuel prices are a fluctuating covariate of interest, representing a potential access barrier to sustained use. Fuel wood is often free to the household because it simply requires that a family member spend time to collect material in the local environs or farms. Increasing LPG prices may lead some families to default to wood use [20, 21]. The research team will track fuel prices by calling or visiting the LPG refueling station on a regular basis. This will allow us to assess individual responsiveness to a dynamic fuel landscape.

